c) Predictive Relationship of BP variability with LV mass and CV morbidity and mortality: Epidemiological studies have shown that repeated measures which account for variation in BP over time offer more precise and less biased estimates of association with CVD and mortality, which are incremental to those obtained from single BP readings.,[50](#_ENREF_50) The variability in BP has various dimensions and is measured using different metrics - ranging from beat-to-beat variability measured with continuous BP recordings to variation in intermittent readings spread over days, weeks, months to years to continuous BP monitoring during sleep and waking hours. In the high risk cohort in COBRA, resting brachial BP was measured at baseline and 6-monthly intervals, two readings at each home visit after 5 minutes of rest between measurements. Thus, two BP readings at each of the four home visits are available during a follow-up of two years on most subjects. In the in-trial analysis of COBRA, the time-series model using all available systolic blood pressures revealed a significant benefit of combined intervention of HHE plus trained GP over no or single intervention, consistent with that based on single follow-up reading at the final 2 year visit. In addition, a trend towards enhancement of the effect of intervention on BP with time was observed (time with treatment effect interaction p=0.02 (unpublished data)). We now wish to explore the association of repeated measures of BP spread over months to years with CVD endpoints of LV mass and CVD morbidity plus all cause mortality. These analyses are likely to unmask the true impact of intervention as they relate to various components of BP and cardiovascular outcomes over time.

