## Ancillary Studies:

- a) To determine the influence of BP and antihypertensive therapy on quality of life in the high risk cohort
- b) To evaluate the use of practice guidelines for management of hypertension among practitioners in the randomized communities.
- c) To examine the relationship between BP variability during 2 years of intervention with LV mass index and cardiovascular morbidity and mortality at 7years.

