# PLAN OF ANALYSIS:

- SAS version 9.13 will be used for analyses.A p value of <0.05 will be considered statistically significant. All analyses will account for clustering at the level of census by household, as this was also the unit of randomization.[62](#_ENREF_62)

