## Ancillary Analysis:

a) For the quality of life study, the mean overall HRQoL score of the high risk cohort will be computed, and compared across randomized groups. Separate multivariable models will be built for the outcome of mean HRQoL score. Linear regression analysis will be performed to determine the association of a) systolic BP at baseline, b) systolic BP at follow-up; c) change in systolic BP from baseline to follow-up with and without adjusting for current use of antihypertensive medications; and b) use of antihypertensive medications. The other candidate predictors will include age, sex, level of education, and socioeconomic status.

b) For the GP survey, the means and proportions of the responses will be compared, as appropriate, for GPs in the clusters randomized to trained GP versus usual care, accounting for clustering by census. The analysis will be done per intention-to-treat as well as per-protocol (restricted to trained GP in relevant clusters).

c) For the assessment of the relationship of BP variability with LV mass and CV morbidity and mortality: BP was measured at baseline and then average of 6-monthly intervals on all high risk trial participants. All available BP readings measured at baseline and 6 monthly intervals during 2 years of intervention on high risk group will be used. We will define four metrics of BP variability based on crude systolic and diastolic BP data: 1) the standard deviation, 2) the coefficient of variation (standard deviation divided by mean BP), 3) variation independent of mean, proportional to SD/mean X, where X will be estimated for each subject by fitting a mixed-effects linear regression model of time on observed BP, which will account for greater fluctuations with higher mean BP.[50](#_ENREF_50),[67](#_ENREF_67)

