We will build multivariable models for the outcomes of LVMI, E/E’ ratio and composite of CVD morbid events and all-cause mortality during 6 years. Candidate BP predictors will include BP variability, absolute baseline BP, mean of all follow-up readings, peak systolic BP achieved during any one of the visits, and episodic stage 2 systolic hypertension (systolic BP >= 160 mm Hg) during these visits. Other predictors will include age, sex, baseline BMI, tobacco use, fasting plasma glucose, and fasting blood lipids. Stepwise forward selection will be used in logistic regression time series analysis with random effects.[68](#_ENREF_68) All analyses will account for treatment assignment and clustering.

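### The variability metric that ancillary aim (c) is about is left to forward selection beside peak systolic BP from the same few visits, so a real but moderate effect can often fail to enter the model

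*Protocol*

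**What the plan says.** The aim, in the Protocol under Ancillary Studies (c), names one exposure: "To examine the relationship between BP variability during 2 years of intervention with LV mass index and cardiovascular morbidity and mortality".

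The analysis, in the Protocol under Ancillary Analysis, lists that exposure as one candidate among several: "Candidate BP predictors will include BP variability, absolute baseline BP, mean of all follow-up readings, peak systolic BP achieved". The list continues with "episodic stage 2 systolic hypertension (systolic BP >= 160 mm Hg) during these visits". The selection rule is "Stepwise forward selection will be used in logistic regression time series analysis with random effects". The only stated commitment about what every model contains is "All analyses will account for treatment assignment and clustering".

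The readings are shared. For the variability metrics, "All available BP readings measured at baseline and 6 monthly intervals during 2 years of intervention on high risk group will be used". The Rationale for ancillary studies adds that "two BP readings at each of the four home visits are available during a follow-up of two years on most subjects". Mean, peak, flag and variability are therefore all computed from essentially the same 4-5 visits.

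The section gives no threshold for entry. The general rule under Plan of Analysis is "A p value of <0.05 will be considered statistically significant".

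**The concern.** When an aim concerns one exposure, its coefficient should be estimated and reported whatever it turns out to be. Here the exposure has to win its place in competition with peak systolic BP, which is nearly a linear function of the mean and SD of the same readings. If both level and variability matter, peak can enter first and take up most of what the variability metric would have explained. The metric then does not enter, and a reader would take its absence as no association.

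If instead all the summaries were kept in one model, the variability coefficient would be taken at fixed mean and fixed peak. That is not the question asked, and the coefficient would be estimated much less precisely. What is at stake is the answer to ancillary aim (c). No randomised comparison is involved.

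**Working it through.** The protocol states no power, effect size or selection probability for this study, so there is no figure to reproduce. The check has three parts.

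**1. How close peak is to mean plus SD.** For k independent normal values the expected maximum above the mean, in population SDs, is 1.029 (k = 4) and 1.163 (k = 5). The metric uses the sample SD, whose expectation is 0.921 (k = 4) or 0.940 (k = 5) of the population SD. The ratio (peak - mean)/SD is independent of SD, so its expectation is

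- k = 4: 1.029 / 0.921 = 1.12
- k = 5: 1.163 / 0.940 = 1.24

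If single readings are used instead of visit values, it is 1.47 for 8 readings and 1.58 for 10.

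**2. Overlap.** In simulated readings, peak regressed on SD, baseline and mean has R² of 0.95-0.98. SD has R² of about 0 on baseline and mean, but 0.78-0.85 once peak and the flag are added. The variance inflation factor is 1/(1 - R²), about 4.6-6.8 from the unrounded R². The standard error of the SD coefficient therefore grows by √4.6 to √6.8, that is 2.1 to 2.6 times. This part needs no assumed effect on the outcome.

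**3. How often variability enters.** Inputs from the protocol: 1341 hypertensive adults with 78% followed at 2 years (1341 × 0.78 = 1046), and 4-5 visits. Assumptions, not in the protocol: mean SBP 148, between-person SD 15-20 and within-person SD 8-14 mm Hg, entry at two-sided p < 0.05, and the effect sizes below. Forward selection was run with the full list and again without peak and the flag, over 120 settings (n = 1046 or 1341; metrics SD, CV and variation independent of mean; continuous outcome). Effects are standardised. Each cell gives the median and range across settings.

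| Mean effect / variability effect | Effect placed on | Full list | Without peak and flag |
|---|---|---|---|
| 0.1 / 0.1 | observed metric | 45% (30-67) | 92% (88-98) |
| 0.1 / 0.1 | underlying SD | 10% (4-24) | 58% (43-80) |
| 0.2 / 0.1 | observed metric | 12% (5-30) | 92% (87-98) |
| 0.2 / 0.1 | underlying SD | 6% (2-9) | 57% (51-74) |
| 0.3 / 0.15 | observed metric | 18% (7-57) | 100% (98-100) |
| 0.3 / 0.15 | underlying SD | 10% (3-26) | 93% (88-98) |
| 0.2 / 0.2 | observed metric | 92% (74-98) | 100% (100-100) |
| 0.2 / 0.2 | underlying SD | 32% (15-42) | 99% (95-100) |

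In 78% of the 120 settings, all with a mean-BP effect, variability entered less than half the time. In round figures, moderate effects give roughly 2-60% against 40-97%; settings at the edge of the grid run somewhat beyond this.

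A logistic outcome with 20% events behaves alike. At log-odds 0.45 for mean and 0.30 for variability, entry is 31% v 97% (observed metric) and 11% v 77% (underlying SD).

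A second setting was scaled to LVMI: 900 people, between- and within-person SDs 14 and 11 mm Hg, residual SD 22 g/m², mean effect 0.3 g/m² per mm Hg.

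- Effect 1.0 per mm Hg of underlying SD: 13% v 85%.
- Effect 0.6 per mm Hg of observed SD: 30-49% v 96-98% over repeated runs.
- Effect 1.0 per mm Hg of observed SD: 97% v 100%.
- Effect 1.0 on underlying SD with no mean-BP effect: 83% v 85%.

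**Which part of the plan causes it.** With SD, mean and baseline forced in and peak and the flag left as candidates, variability was detected in 82% of runs, against 85% with the short list. Removing the flag while keeping peak changed entry by at most 3 percentage points.

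**The case against.** A reader might infer that a real variability effect would usually be lost and that the aim will go unanswered. The documents do not support that. They give no effect sizes and no within-person SD. With no mean-BP effect, or a large effect of the observed metric, almost nothing is lost. With the mean-BP effect lowered to 0.1 g/m² per mm Hg, variability still entered in 53-60% of runs. With a much wider spread of variability between people (log-SD 0.5), it entered in 75-85%.

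A reader might also blame the candidate list alone, or the >=160 flag as much as peak. Neither holds. Forcing the exposure in restores detection even with peak still a candidate, and the flag adds little beyond peak.

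Three further points on the other side are fair. The text speaks of models in the plural and does not say outright that every BP summary enters one pool. The rationale is exploratory and mentions several components of BP, so comparing them may be intended. Details of forced terms could sit in an analysis plan that is not shown.

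These soften the point but do not remove it. The protocol does fix the candidate list and forward selection, and it keeps no BP term in the model. Comparing components is a legitimate aim, but selection among near-collinear summaries of a few readings cannot show which one matters; separate models can. The no-mean-effect case also sits badly with the protocol's own rationale, which treats raised LV mass as an established consequence of uncontrolled hypertension.

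**Conclusion.** The point stands in conditional form. The main fault is that the exposure named in the aim is left to stepwise selection. Peak systolic BP is the competitor that makes this costly, because it carries level and variability together.

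The roughly two-fold or greater rise in standard error when all the summaries share a model follows from the overlap alone. The entry rates do not: they rest on assumed BP spread, effect sizes and an entry threshold of 0.05. Covariates, treatment assignment and random cluster effects were not modelled. A moderate variability effect alongside a mean-BP effect is the situation in which the metric often fails to enter; it is plausible here but not established.

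The point is confined to ancillary study (c) and does not touch the primary or secondary outcomes. It deserves correction because following the stated rule gives a worse answer to the stated question and the remedy is cheap.

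**What to change.** In Ancillary Analysis (c), state that every model contains baseline SBP, mean follow-up SBP and one variability metric, in addition to treatment assignment and clustering. Fit one model per metric. Report the variability coefficient with its 95% confidence interval whatever its p-value. Any selection should apply only to the other covariates.

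Examine peak SBP, and with less impact the >=160 mm Hg flag, in separate models so that they do not compete with the variability metric. Forcing variability in alongside baseline and mean gave essentially the same detection as removing the competitors (85-100% with the effect on the observed metric, 45-100% on the underlying SD).

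The cost is a few sentences of protocol or analysis-plan wording and a few more models to report. No new data are needed.

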## Ethical Considerations

Ethical approval will be sought from the Ethics Review Committee at the Aga Khan University. Informed consent will be obtained from each adult and, where children are involved, assent from the child and consent from parents prior to enrolment.

All participants enrolled in the main COBRA trial will be included in the study for follow-up. However, the individuals (children or individuals aged 15 – 39 years) not enrolled in the main study, pregnant women, bed ridden and/or mentally retarded study subjects unable to consent will be excluded.

Since, this is a follow-up study on the participants enrolled earlier in the main study, there are no major ethical issues in this follow-up study. However, we will make sure that following normal ethical issues should be dealt ethically:

- Written consent and assent will be obtained from adults and children participants respectively.
- It would be made clear to each and every participant that he/she is free to decide whether or not to participate in this follow-up study.
- The participants will be briefed about the nature of the study, the interview technique, the potential nature of use of the information collected, type of medical examination performed and the type of investigations taken.
- He/she will be free to withdraw from this study at any time without giving any reason for withdrawing.
- The expenses for the all laboratory tests performed during this follow-up will be covered by the study.
- Study participants unwilling for laboratory tests will not be forced for blood / urine sampling.
- The participants with cardiovascular events during the study will be assessed and advised by study cardiologist /neurologists for management of complication and prevention of future events.
- If high BP with headache or chest pain or shortness of breath or dizziness or blurred vision or any other active disease is diagnosed during assessment, the participant will be referred to the hospital for appropriate management. A referral letter and copy of laboratory tests will be provided.

*Confidentiality of the subjects:*

- All the collected identifiable information and reports will be kept confidential in a secure locked space.
- All filled questionnaires would be kept in secure space with restricted access exclusively to key research team members (PI, coordinator, and data manager).
- Electronic copies of the complete data will be stored in password protected data files.
- Only anonymized and de-linked data will be shared with research team members for analysis.

*Risk and benefits to the study subjects:*

No adverse effects / risks are expected as this is an observational follow-up without any intervention. The study subjects will have the same benefits as those of main study, i.e.

- All participants during follow-up will have their free physical assessment and advice for follow-up with appropriate referral to a family health care provider.
- The subjects enrolled during the follow-up would be evaluated for hypertension, coronary artery disease diabetes, dyslipidemia and albuminuria through blood and urine tests.
- The cost of all blood and urine tests, and echocardiography performed during this follow-up will be covered by the study.
- The reports will be communicated to them along with appropriate advice.
- The participants with positive cardiovascular events will have their assessment by cardiologist / neurologist free of charge. Moreover, they will have a free pick and drop facility.

# TIME LINE:

Protocol development, and ethics approval: 3 months, implementation and data collection 12 months; analysis; 9 months (aims 1 & 2: 4 months; aims 3 & 4: 4 months).

**
[figure not shown]
**

